## Abstract

Parental relationship dissolution is among the most prevalent life crises for youths and is associated with both short- and long-term intra- and interpersonal struggles. Extant support programs tend to be in-person and in a group format. However, the structure and personnel needed for these programs make them costly to implement, less accessible, and difficult to scale. Digital interventions may present a suitable alternative. The current study examines the effectiveness of an online psycho-social intervention for children who have experienced parental relationship dissolution in Denmark, using a two-arm, parallel-group, randomized controlled trial study design. Families are recruited through Danish municipalities and the Danish Agency of Family Law and randomly assigned to the intervention group or wait-list control group. Individuals are assessed at baseline, 4 weeks, and 12 weeks post-baseline; parents complete questionnaires on behalf of their children aged 3–10, while youth aged 11–17 complete the questionnaires themselves. The primary study outcomes are 1) emotional problems symptoms, as measured by the Strength and Difficulty Questionnaire (SDQ), 2) mental well-being related difficulties, represented by the SDQ-Total scale score, and 3) impact of problems on daily life, as assessed by the SDQ-Impact scale score, at 12-weeks post-baseline. The data will be analyzed using a generalized estimating equation, accounting for non-independence of data (nesting of children within a family). The present study will contribute to the extant knowledge about the effectiveness of digital interventions for youths experiencing parental relationship dissolution and contribute to a cost-effective evidence-based scalable psychological help for a population who needs it.

Parental relationship dissolution is among the most prevalent life crises for youths (Boring et al., 2015). In Denmark, 22 % of all youths living with their parents are split between two households, and annually 24.000 youths transition from living in a nuclear family to other types of living arrangements (Statistics Denmark, 2018). Research shows that parental relationship dissolution is negatively associated with youths' mental well-being, quality of life, and social and academic development (Amato, 2001, Amato, 2014; Amato and Keith, 1991; Kunz, 2001), including learning difficulties, lower self-esteem, poorer relationships with parents and friends, and symptoms of depression, anxiety, behavioral problems, and risky health behaviors, both in the short term and in the long term (Auersperg et al., 2019; Fallesen et al., 2023; Kunz, 2001; Størksen et al., 2005). Consequently, there is a need for effective, scalable, and accessible interventions for youths.

Many post-divorce interventions have been developed to help adults and children cope with a divorce. Those aimed at parents have tended to yield positive intra-personal outcomes for the adults themselves as well as improved parental cooperation and co-parenting (e.g., Saini and Corrente, 2024). These programs also appear to have some downstream positive effects in terms of improved child adjustment post-divorce (Fackrell et al., 2011; Saini and Corrente, 2024). Several preventive interventions have also been developed directly targeting youths experiencing parental relationship dissolution, such as Children's Support Group (CSG) (Stolberg and Garrison, 1985), Children of Divorce Intervention Program (CODIP) (Pedro-Carroll and Cowen, 1985), and Kids in Divorce Situations (KIDS) (Pelleboer-Gunnink et al., 2015). These programs are often based on psychoeducational and cognitive-behavioral principles and are facilitated in a group format led by a coach or therapist. Studies of these programs have yielded positive results in improving internalizing and externalizing problems (Haine et al., 2003; Pruett and Barker, 2010). However, the structure and personnel needed for these programs make them costly to implement, less accessible, and difficult to scale. More generally, meta-analyses and narrative reviews suggest that the effects of these programs are varied. Poli et al. (2017) found that, overall, group-based programs for children with divorced or separated parents appear to yield positive outcomes in terms of self/individual level variables (e.g., self-esteem and anxiety), family (e.g., parent-child relations) and interpersonal (e.g., social skills) relations, school (e.g., academic performance) and behavior (e.g., behavioral problems) (Poli et al., 2017). Stathakos and Roehrle (2003) showed that intervention programs for youths experiencing relationship dissolution were efficacious in reducing anxiety and depression symptoms and improving academic behavior and performance, with a medium average effect size (*d* = 0.43). However, only around half of the studies were judged to be of high methodological quality and those studies showed a lower average effect (*d* = 0.32) (Stathakos and Roehrle, 2003). Interestingly, they also showed that the interventions were most effective when the interventions were implemented early (i.e., within 30 months of the divorce), and when the interventions were less comprehensive (i.e., fewer and shorter sessions) (Stathakos and Roehrle, 2003). Conversely, a more recent meta-analysis by Herrero et al. (2023) demonstrated overall small and statistically non-significant effects on children's internalizing (e.g., depression, anxiety) and externalizing (i.e., aggressiveness, behavioral problems, learning problems, and negative peer relationships) symptoms, but medium to large and robust effects in terms of children's self-esteem and divorce adjustment (Hedge's *g* = 0.56–0.70). Moreover, the analyses also suggested some heterogeneity in effects, and some evidence of indirect effects, such that studies with greater changes in internalizing symptoms reported greater changes in externalizing symptoms.

Digital interventions are often more affordable, easier to scale, and have the ability to be updated and expanded (Kazdin and Blase, 2011). Digital interventions may also be preferred by people experiencing relationship dissolution, as they can be more convenient, accessible anytime anywhere, and help reduce stigmatization (Bowers et al., 2011; Greenberg et al., 2019). Recent research shows that digital interventions for distressed couples and adults undergoing relationship dissolution and divorce yield moderate to large effects (Doss et al., 2016; Hald et al., 2020a). However, there is a dearth of research-based digital interventions aimed at youths (Bowers et al., 2014; Haine et al., 2003). To our knowledge, there is only one digital intervention aimed directly at youths of divorced parents, namely the Children of Divorce-Coping with Divorce (CoD-CoD) (Boring et al., 2015), with another under development (O'Hara et al., 2023). The CoD-CoD intervention consists of five self-paced modules, adapted from evidence-based cognitive–behavioral coping programs for adolescents (aged 11–16 years) (Boring et al., 2015). Evaluations of the CoD-CoD interventions showed that the intervention was successful in reducing youth-reported mental health problems and adjustment problems among youths experiencing parental relationship dissolution and also among youths experiencing high levels of parental conflict (Boring et al., 2015; O'Hara et al., 2022). Although the CoD-CoD has demonstrated promising results, the CoD-CoD has only been developed for and tested among older youths. The intervention currently under development (O'Hara et al., 2023) tests 3 digital modules focused on teaching coping skills (i.e., reappraisal, distraction, and relaxation) to help children cope with a high-conflict parental divorce. However, similar to CoD-CoD, the intervention only targets a small subset of children, specifically those aged 9 to 12. As relationship dissolution affects youths across different ages (Pedro-Carroll, 2005), it is imperative to develop interventions that can encompass and be scaled to multiple age groups.

The current study evaluates the efficacy of a newly developed digital intervention program for youths experiencing parental relationship dissolution, named Cooperation After Divorce – NXT (abbreviated ‘SES NXT’ as Cooperation After Divorce = ‘Samarbejde Efter Skilsmisse’ in Danish). The SES NXT intervention is a brief, modular and age-adjusted intervention developed in line with the most prevailing theory in divorce research, namely the Divorce-Stress-Adjustment Perspective (DSAP) (Amato, 2000). Divorce is understood as a process that exposes the child to several stress factors, which can have a cumulatively negative effect on the child over time. These stress factors may include parental conflict, difficulty communicating with parents, navigating new home environments, and perhaps new ‘bonus’ families (Amato, 2014; Ottosen et al., 2018). The extent to which the youth is affected by the parental relationship dissolution, and the long-term consequences thereof, is related to the balance between these stressors, the youth's psychological make-up, and the youth's access to key protective factors, such as good coping skills (O'Hara et al., 2019), good child-parent relations and communication (Gunter Castleton, 2020; Seijo et al., 2016), and the interpretation and meaning made of the dissolution (e.g., loss, gain, change, healing) (Brand et al., 2017).

Thus, the objective of this present study is to examine whether the SES NXT intervention is effective in improving mental and physical health and well-being among youth and children, aged 3 to 17 years, who have experienced parental relationship dissolution. The study employs a randomized controlled trial (RCT) design, with assessments at baseline (T1), 4 weeks post-baseline (T2), and 12 weeks post-baseline (T3), comparing an intervention group, who will receive unlimited access to the SES NXT intervention, to a waitlist control group, who will not. We have developed the following primary study hypotheses:H1) The intervention group will report a significantly lower SDQ emotional symptoms score than the control group at 12 weeks follow-up (T3).H2) The intervention group will report a significantly lower overall SDQ difficulty score than the control group at T3.H3) The intervention group will report a significantly lower SDQ impact score than the control group at T3.

We also developed the following secondary hypotheses:H4–7) Compared to the control group, the intervention group will report significantly lower scores in terms of conduct problems (H4), hyperactivity/inattention (H5), and peer relationship problems (H6), and higher levels of prosocial behavior (H7) at T3.H8) The intervention group will report significantly higher levels of quality of life than the control group at T3.H9–11) The intervention group will report significantly less frequent headache, abdominal pain, and nausea (H9), less body image dissatisfaction (H10), and fewer sleep problems (H11) than the control group at T3.H12–14) Compared to the control group, the intervention group will report significantly higher scores in terms of frequency of communicating needs (H12), setting boundaries (H13), and connecting with adults (H14) at T3.H15) The intervention group will report significantly less school non-attendance than the control group (H15) at T3.

## Methods

1

We have created an Open Science Framework project (https://osf.io/wusjk/?view_only=6fbd7713834a4580bff061b5d92f7495), which contains study-relevant documents, such as the measures document and codebook, with both English and Danish language versions of the items, power simulation code, the intervention white paper (detailing the intervention content), and additional methodological information.

### Eligibility criteria and sample size

1.1

To be eligible to participate, parents must have at least one custodial child between the ages of 3 and 17, as well as an electronic device (phone, tablet, or computer) with access to the internet. Parents, and their children, must be able to read and understand Danish, as all materials are provided in Danish only.

We simulated the data structure and assumed moments (mean difference and outcome pooled standard deviation) to determine the minimum sample size for this study using R, version 4.4.1. The sample size was calculated with reference to the primary hypothesis (H1), assuming a power of 90 % and an alpha level of 0.05. The estimate of the outcome pooled standard deviation was based on the post-test results from Pelleboer-Gunnink et al.'s (2015) study of a school-based intervention for children of divorce, which also used the emotional symptoms subscale from the SDQ as a primary outcome. We expected a small to moderate effect, as evidenced by a raw mean difference of 0.40 in the SDQ emotional subscale score between the intervention and control group. The test of relevance is a cross-sectional multi-level model, with children nested within parent. We used a generalized estimating equation (GEE), as these make fewer distributional assumptions and yield more robust standard errors. With these parameters, the simulation suggested that roughly 700 clusters (parents with children) would be needed. Enrollment into the study began on May 1st, 2023, and will close when the target sample is reached or on August 31st, 2024, whichever comes first.

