## Discussion

2

Developing an effective intervention for youths experiencing parental relationship dissolution is of critical importance, as a great number of youths experience negative short- and long-term consequences relating to a breakup between their parents. The digital SES NXT intervention covers a wide range of topics in a media-rich environment, is tailored to the age of the child, and is scalable. Strengths of the study include the use of sound psychometric measures, and the inclusion of family units (i.e., parent and children), as opposed to individual children, in a study with an RCT design. Potential limitations include issues relating to the completion of surveys by 11- to 17-year-olds, who may not receive the links to the surveys in cases of parents providing their own e-mail address and phone number, or who may simply elect to not complete the survey. Moreover, the online nature of the study limits us from assuring that children aged 11 to 17 complete the survey in privacy. It may be that some of the children complete the survey together with their parent; the parental presence may influence the child's responses in various ways such that the responses do not reflect their true feelings and thoughts. For instance, it may be that children alter their responses to please their parents, to not worry them, or to gain additional attention from them. Technical breakdowns and outages may also occur, such that participants cannot access the intervention. We will regularly check and monitor the technical systems to ensure that the intervention website does not crash or become unavailable and that the API (application programming interface) that connects the various electronic systems works correctly, to minimize the risk of breakdowns. Moreover, there will be a support phone number and e-mail address that participants can contact to report technical issues and receive help. Furthermore, there may be self-selection into the study, as many studies have found that those with better health, higher education and income, and of female gender are more likely to seek treatment (Wellstead, 2011) and to participate in research studies (Søgaard et al., 2004).

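### The sample-size section lists no allowance for missing week-12 data, yet 700 families appears to be the enrolment target, so the stated 90% power needs qualifying

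*Protocol article*

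**What the plan says.** All the sizing information is in Eligibility criteria and sample size (1.1). The calculation is a simulation tied to H1, "assuming a power of 90 % and an alpha level of 0.05". The effect is "a raw mean difference of 0.40 in the SDQ emotional subscale score between the intervention and control group". For the spread, "The estimate of the outcome pooled standard deviation was based on the post-test results from" a cited school-based study; the value is not printed. The test is a cross-sectional GEE with children nested in parent. From these inputs "the simulation suggested that roughly 700 clusters (parents with children) would be needed", and the section presents the result as a minimum. Enrolment "will close when the target sample is reached or on August 31st, 2024, whichever comes first". No other sample number appears, and no attrition rate or inflation step is mentioned.

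Other sections anticipate loss:

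- **Procedure (1.3):** families are randomised and then sent the T1 links. Follow-up surveys go out only once T1 is completed, so a randomised child without T1 gets no T3 survey. Reminders and movie tickets are used to support retention.
- **Statistical analyses (1.6):** an attrition analysis and multiple imputation are planned. The H1 model also includes the baseline score of the outcome.
- **Discussion (2):** 11- to 17-year-olds may not receive the survey links, "or who may simply elect to not complete the survey".

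**The concern.** A cross-sectional comparison at T3 draws its information from children with a T3 outcome. If 700 families are the minimum for 90% power in that comparison, and recruitment stops once 700 are enrolled, any loss of families before T3 leaves the comparison below its own minimum under the model used to size it. The article gives the chain from inputs to sample size to closing enrolment without saying which families are counted: signed up, randomised, with T1, or with T3.

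What is at stake is how H1 is read. The published 90% is the natural yardstick for a null result, and it may not describe the number of families that actually contribute week-12 data.

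**Working it through.** **Inputs from the article.** Mean difference 0.40; alpha 0.05; power 90%; 1:1 allocation by family; roughly 700 families, so 350 per arm.

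**Inputs not in the article.** The SD, children per family, intra-family correlation (ICC), T3 response and sidedness. I take a two-sided test and give the one-sided result as a check.

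**Step 1: the plan's own figure.** 700 cannot be reproduced, because the SD, cluster size and ICC are not printed. It can only be back-solved. With one child per family and no loss,

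SD = 0.40 / [(1.960 + 1.282) × √(2/350)] ≈ 1.63.

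With 1.3 to 2 children per family and ICC 0.1 to 0.5 (both assumed), the implied child-level SD is about 1.74 to 2.20. So 700 is consistent with a calculation that contains no inflation for loss, but this does not prove it.

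**Step 2: power under the sizing model when families are lost.** Calibrating to 90% at 700 removes the need for the SD and ICC. If a fraction L of whole families has no T3 data,

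Power = Φ(3.2415 × √(1 − L) − 1.960).

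At L = 0.20: 3.2415 × 0.8944 − 1.960 = 0.939, and Φ(0.939) = 0.826.

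| Families lost by T3 | Families with T3 data | Power, two-sided | Power, one-sided |
|---|---|---|---|
| 0% | 700 | 90.0% | 90.0% |
| 5% | 665 | 88.5% | not computed |
| 10% | 630 | 86.8% | 87.1% |
| 20% | 560 | 82.6% | 83.5% |
| 30% | 490 | 77.4% | 78.9% |
| 40% | 420 | 70.9% | 73.3% |

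**Step 3: credit for the planned baseline adjustment.** If the baseline score explains a share R² of the outcome variance, the residual variance is multiplied by 1 − R²:

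Power = Φ(3.2415 × √[(1 − L)/(1 − R²)] − 1.960).

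Power equals 90% when 1 − L = 1 − R², so break-even loss is R² itself. The article gives no baseline correlation; the values below are assumptions.

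| Families lost | R² = 0.09 | R² = 0.25 | R² = 0.36 |
|---|---|---|---|
| 10% | 89.7% | 94.4% | 97.0% |
| 20% | 86.0% | 91.7% | 95.2% |
| 30% | 81.1% | 87.9% | 92.4% |
| 40% | 74.9% | 82.6% | 88.1% |

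The adjustment is not among the inputs listed in 1.1, which takes its SD from post-test results. The printed 90% therefore does not visibly take credit for it.

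**The case against.** The strongest reply is that silence is not proof. The article says the data structure was simulated as well as the moments, and Methods places the simulation code in a public repository that is not shown here. That structure could include missing data. This stands: the documents show that no loss allowance is stated, not that none was made. It is also an inference that 700 is the enrolment target, since 1.1 speaks only of a target sample. It is the likeliest reading because no other number is given.

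A reader might go further and infer that the 90% holds only if every family supplies T3 data. The documents do not support that. Even unadjusted, 5% loss costs only 1.5 points. With the planned adjustment at an assumed R² of 0.25, power is still about 92% with one family in five lost. T2 outcomes are collected and could let imputation recover part of the missing information, though not all of it. The non-completion named in the Discussion concerns individual youths, and losing one sibling costs less than losing the family.

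A reader might also use the back-solved SD to argue that the effect is smaller than the article's description of it. That does not hold either. It rests on assumed cluster sizes and correlations, and on 700 containing no inflation, which is the open question.

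It may also be said that an article can leave the SD, ICC and cluster size to deposited code. I agree, and their absence is not the point. What 700 counts, and what T3 loss it assumes, cannot be left open in the same way, because 1.1 itself gives the figure, the power and the rule for closing enrolment.

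**Conclusion.** The point holds as a badly fixed figure; no stated number is shown to be miscalculated. Section 1.1 attaches 90% power to roughly 700 families using inputs that list no T3 non-response, and 700 appears to be where enrolment stops, in a trial that expects loss both before T1 and by T3. Under the listed model, 10 to 40% loss of whole families means about 87% down to 71% power. Under the adjusted model of 1.6 the shortfall is smaller, and it disappears while loss stays below the variance explained.

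This rests on a two-sided test, whole-family loss at random, exact 90% power at 700, and assumed values for R². It would fall away if the deposited code already models loss; the article would then need only to say so.

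**What to change.** In 1.1, state that 700 is the number of families with T3 data needed for 90% power on H1. If the simulation already includes loss, state the T3 loss it assumed and that 700 is the number enrolled.

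Then restate H1 power at 700 randomised families over a range of T3 response, for example 60 to 90%. Rerun the existing simulation code with non-response added and with the baseline-adjusted model of 1.6. The rerun can also distinguish loss of whole families from loss of single children.

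The cost is one rerun and a sentence or two. No extra recruitment is asked for. The downside is that the stated power may become less favourable.

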### Ethical approval and protocol registration

1.2

All procedures are in accordance with the ethical standards of the institutional and national research committee and with the 1964 Declaration of Helsinki and its later amendments or comparable ethical standards. We have received ethical approval from the University of Copenhagen Research Ethics Committee for Science and Health (case number 504–0290/21–5000), and from the Danish Data Protections Agency (case number 514–0699/22–3000). The study is exempt from further ethical evaluations following the rules and regulations as set forth by the Scientific Ethical Committees of Denmark (i.e., national ethics approval was not required). The protocol was registered with clinicaltrials.gov prior to data collection (ClinicalTrials.gov Identifier: NCT05760820).

